## 4.5 Analysis Populations

The Enrolled set will include all patients who have provided informed consent and have been included into the study data base.

The intention-to-treat (ITT) analysis set will include all patients randomly assigned to a treatment group, who started with the treatment, regardless of whether they completed the treatment or adhered to the protocol.

The modified intention-to-treat (mITT) analysis set will include all patients who were randomly assigned to a treatment group with at least 6 weeks of follow-up data (i.e., those who attended the first clinical follow-up visit).

The Per Protocol (PP) Analysis Set will include all randomised patients meeting the study eligibility criteria who completed the 52 weeks follow-up. (i.e., those who attended the final study visit).

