## **8.3 Study procedures**

This study will be a prospective non-inferiority trial with two randomized groups. The patients will be screened, included and randomized at the outpatient clinic of the participating hospital departments. One group of patients will use the reusable catheter and the control group will use the single use catheters. After inclusion, the patients will be followed up for a period of twelve months. See chapter 3 'Study design' for the precise follow up schedule.

There will be two extra clinical consults and seven telephone consults when participating in this study. Patients will receive a financial compensation for the expenses of traveling to the hospital for the clinical consultations.

Tracking UTIs and hospital admissions will be performed by status analysis by the researchers of the trial and patients will track their infections using a diary. Active cooperation of the involved consultants and continence nurses is asked when the participating centers are included in the trial. For the contact moments, standardized

questions will be provided in Gemstracker, so all patients will be asked the same questions and data will be as complete and similar as possible.

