#### 2.2.2 Control settings (if applicable)

Patients allocated to the control arm will remain using their own single-use catheters, the choice of the single-use catheter will be determined by the preference of the patient.

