## 6 Analysis Methods

### 6.1 Methods for Primary Outcome

#### 6.1.1 Descriptive Statistics

All categorical (binary and ordinal) data will be summarised using frequency counts and percentages of patient incidence. Percentages will be calculated using the study population (FAS); any exceptions to this will be highlighted in the table footnote. The continuous variables will be summarised using number of patients (N), mean, standard deviation (SD), median, 25/75 percentile and range

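### No analysis set is named for the non-inferiority test, none of the sets offered for analysis is all patients as randomised, and the narrower ones can drop reusable-arm patients who leave early after an infection

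*Combined protocol and SAP*

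**What the plan says.** SAP 4.5 offers three sets for comparing the arms, plus an Enrolled set to which no analysis is attached.

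- ITT: "The intention-to-treat (ITT) analysis set will include all patients randomly assigned to a treatment group, who started with the treatment"; completion and adherence do not matter.
- Modified ITT (mITT): randomised patients "with at least 6 weeks of follow-up data (i.e., those who attended the first clinical follow-up visit").
- Per protocol (PP): this set "will include all randomised patients meeting the study eligibility criteria who completed the 52 weeks follow-up". SAP 4.4.2 defines PP differently. It also excludes patients who stop the intervention before 52 weeks, who exceed 20% single-use catheterisations in the reusable arm, or who develop a new exclusion criterion.

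SAP 6.1.2 (primary analysis), SAP 3.3.3 (decision rule) and protocol 10.1 name no set. SAP 6.1.1 says "Percentages will be calculated using the study population (FAS"), but FAS is not defined in SAP 4.5. The flow diagram in SAP 4.1 provides for randomised patients left out of the primary analysis, with reasons reported but no rule for leaving them out.

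On the control arm, SAP 2.2.2 states: "Patients allocated to the control arm will remain using their own single-use catheters". Protocol 8.4.1 removes patients whose cleaning technique stays incorrect after retraining. Protocol 8.6 ends follow-up at any withdrawal, and SAP 6.1.3 rules out imputation.

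On visits, protocol 8.3 states: "There will be two extra clinical consults and seven telephone consults when participating in this study". The schedule in protocol section 3 places the clinical visits at weeks 0 and 52 and makes week 6 a telephone call. SAP 3.4 labels week 6 KC2, a clinical consult.

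**The concern.** In a non-inferiority trial, losing poor outcomes from the experimental arm moves the result towards success. Two separate rules could do this.

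First, the start condition in ITT is not neutral between arms. A control patient carries on as before and has started by default. A reusable-arm patient has to begin a new device and can fail to do so.

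Second, mITT and PP require a minimum stay in the study. A reusable-arm patient who starts, has an infection in the first weeks and leaves remains in the SAP's ITT set but disappears from mITT and PP. The trial is unblinded, and the withdrawal rule for faulty cleaning can apply only to the reusable arm. Protocol 13.2 links that rule to infection risk. Infection-related early loss is therefore plausibly more frequent in that arm.

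Because no set is named, the choice could be made after the data are seen. The primary outcome is total UTIs over total follow-up time, so a patient with short follow-up can contribute what was observed, and brevity alone is no reason for exclusion.

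The mITT gloss adds a further ambiguity. Read against the protocol's visit schedule, the first clinical visit after baseline is week 52, which would reduce mITT to completers.

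**Working it through.** The plan prints no figure for this point. Its rate-based sample size supplies the inputs, so I reproduced that first. (1.960 + 0.842)² = 7.849, and 7.849 × 2 × 0.21² / 0.0675² = 151.9, so 152 per arm as stated. This uses 50% of the mean of 0.13 and 0.14, that is 0.0675; the printed 0.07 would give 142. The adopted size is 154 / 0.80 = 192.5, so 193 per arm and 386 in total.

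**Inputs.** From the documents: 193 per arm, control rate 0.13 per month, SD 0.21, 12 months of follow-up, margin 0.07, one-sided 0.025. Assumed:
- the reusable rate is 0.20, exactly at the margin, so any claim of non-inferiority is false;
- a share q of reusable-arm patients with at least one UTI in the first 6 weeks (W = 6 × 12/52 = 1.385 months) leaves at week 6;
- no controls leave;
- each patient's own rate is constant, including after leaving.

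**Model.** Patient rates follow a gamma distribution and counts are Poisson. Holding the SD of the 12-month rate at 0.21 gives a between-patient variance of 0.21² − mean/12.
- Control: 0.0441 − 0.0108 = 0.0333; shape 0.13²/0.0333 = 0.508.
- Reusable: 0.0441 − 0.0167 = 0.0274; shape 0.20²/0.0274 = 1.458; scale 0.0274/0.20 = 0.137.

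**Who is at risk of exclusion.** In the reusable arm, P(UTI in the first 6 weeks) = 1 − (1 + 0.137 × 1.385)^−1.458 = 0.224. With q = 25% or 50%, 5.6% or 11.2% of the arm leaves, about 11 or 22 of 193 patients.

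**Expected shift, by hand.** Over 12 months, patients with an early UTI average 0.378 per month and the others 0.149 (0.224 × 0.378 + 0.776 × 0.149 = 0.200).
- mITT, q = 25%: (0.776 × 0.149 + 0.75 × 0.224 × 0.378) / (1 − 0.056) = 0.189, a difference of 0.06 from 0.13.
- mITT, q = 50%: 0.178, a difference of 0.048.

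**Simulated error rate** (6,000 runs per row, normal-theory interval in place of the bootstrap):

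| q | Share of reusable arm leaving | Mean difference in mITT | False NI: mITT | False NI: kept, cut at week 6 | False NI: followed to 12 months |
|---|---|---|---|---|---|
| 0% | 0% | 0.070 | 2.5% | 2.5% | 2.5% |
| 10% | 2.2% | 0.066 | 3.6% | 3.0% | 2.3% |
| 25% | 5.6% | 0.060 | 6.3% | 4.1% | 2.0% |
| 50% | 11.2% | 0.047 | 18.2% | 8.3% | 2.2% |
| 75% | 16.8% | 0.034 | 41.9% | 14.8% | 2.5% |

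Repeat simulations with the same inputs put the mITT figures at 6.3 to 7% for q = 25% and 18 to 19% for q = 50%. The column headed kept, cut at week 6 is what the SAP's ITT set delivers for patients who started, given protocol 8.6. Every row fits within the 20% dropout that the plan expects, which it does not split by arm.

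**The case against.** The strongest reply is that the two rules should not be run together. The SAP's ITT set drops only patients who never start; those who start and fail early are kept. Non-starters are not early failures, their number is unknown, and training takes place at the baseline visit, so there may be few. This is right, and the point is worded accordingly.

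A reader might go further and infer that early failures will be dropped almost only from the reusable arm. The documents do not support that. The mITT rule reads the same for both arms, any patient may withdraw at any time, and no early-loss figure by arm is given. That controls continue unchanged and that cleaning withdrawals affect one arm makes an imbalance plausible, not established. Nor is the direction of bias certain: it requires that leavers have higher UTI rates. Leaving for inconvenience unrelated to infection would not shift the rate in this way.

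A reader might also arrive at larger error rates, about 12% and 33 to 35% for q = 25% and 50%. Those need gamma shape 0.555 in both arms, which implies an SD of √(0.20/12 + 0.20²/0.555) = 0.298 in the reusable arm rather than the plan's 0.21.

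Finally, redefining ITT does not by itself restore the nominal level, because follow-up still ends at withdrawal. That stands and shapes the fix.

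**Conclusion.** The point holds in this form. The ITT set carries a start condition that in practice only the reusable arm can fail. mITT and PP can drop patients who leave early after an infection. No set is assigned to the non-inferiority test, FAS is undefined, PP has two definitions, and the mITT gloss conflicts with the protocol's visit schedule.

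At a true difference equal to the margin, losing about 6% or 11% of the reusable arm in this way gives false non-inferiority of about 7% or 18% in mITT, and about 4% or 8% when the same patients are kept with follow-up cut at week 6. These are illustrations that assume an SD of 0.21 in each arm, no early control loss, and loss confined to patients with an early UTI; they are not forecasts. The 2% obtained with full follow-up also assumes that a patient's rate does not change after stopping. If a return to single-use lowers it, the ITT difference shrinks, which is one reason to report a PP result alongside.

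The undefined choice of set needs no assumption: it is on the page and could decide the conclusion, so it should be settled before the data are analysed.

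**What to change.** In the SAP:
- Define ITT as all randomised patients, analysed as allocated, with person-time counted from randomisation and no start or minimum follow-up condition.
- Name it as the primary set in 6.1.2 and 3.3.3, and replace FAS in 6.1.1 with it.
- Make mITT a sensitivity analysis and define it by follow-up time. Reconcile the week-6 contact between SAP 3.4 and 4.5 and protocol sections 3 and 8.3.
- Reconcile the PP definitions in 4.4.2 and 4.5 and report PP as supportive. This matters more once follow-up continues after stopping: a patient who stopped the reusable catheter but was followed to week 52 would be in PP under 4.5 and out under 4.4.2.

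In the protocol: amend 8.6 so that, with the patient's consent, UTIs continue to be recorded to week 52 after the allocated catheter is stopped. This concerns data collection only, not which catheter the patient then uses.

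The cost is SAP wording plus a small protocol amendment. The extra data can come from the telephone contacts, patient diary and record review already planned. The sample size stays at 386.

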## 5 Outcome Definitions

### 5.1 General Definitions and Derived Variables

#### 5.1.1 Body Mass Index (BMI)

Body Mass Index (BMI) = Body weight in kilograms divided by the square of the height in meters.

#### 5.1.2 Urine cultures

Urine samples are obtained and cultured at inclusion (week 0) and final visit (week 52). Significant bacteriuria and thereby a positive urine culture was defined by microbial growth of  $\geq 10^3$  cfu/mL of one or more bacterial species in a single catheter urine specimen or in a mid-stream voided urine specimen, following the European Urology Guidelines on Urological Infections.

#### 5.1.3 Other calculations

Age (years) = [(date of baseline – date of birth)/365.25]

Time of event = day of event – day of randomization

### 5.2 Primary Outcome Definition

The primary outcome is the monthly incidence of UTIs during the study period. The definition of a UTI used for this trial is based on the criteria of Woodford et al (1), on the basis of the EAU guidelines on Neurourology (2) and on the basis of the NHG Guidelines for general practitioners (3).

An UTI is defined by the following two criteria:

1. An acute onset of one or more of the following symptoms: dysuria/pain during catheterization, hematuria, urinary frequency, urinary urgency, suprapubic pain, flank pain, fever ( $>38^{\circ}\text{C}$ ), rigors, and delirium. In case of a neurogenic bladder: a change in specific symptoms, like increased urinary incontinence, limb spasm and autonomic dysregulation, could be indicative for a UTI.
2. One of the following positive diagnostic tests: urine culture, dipslide, nitrite test, or urine sediment analysis.

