## 8. METHODS

### 8.1 Study parameters/endpoints

#### 8.1.1 Main study parameter/endpoint

The main outcome parameters are symptomatic urinary tract infection (sUTI) and hospital admission due to this sUTI. The definition of a sUTI used for this trial is based on the criteria of Woodford et al (29), on the basis of the EAU guidelines on Neurourology (3) and on the basis of the NHG Guidelines for general practitioners (27).

1. Symptomatic UTI (sUTI): A patient with an acute onset of one or more of the following symptoms: dysuria/pain during catheterization, hematuria, frequency, urgency, urinary retention, suprapubic pain, flank pain, fever, delirium or rigors who did not have a negative urine culture result or a negative nitrite test or a negative dipslide/urine sediment (when taken before receiving antibiotics) or a positive blood culture for a known uropathogen. Additionally, in patients with neurogenic bladder a change in specific symptoms, like increase in incontinence, limb spasm and autonomic dysregulation, could be indicative for a sUTI. The diagnosis is to be decided by the local consultant involved in study.

2. Bacteremic UTI (bUTI): A patient with a blood culture positive for a known uropathogen, providing that their urine culture was not negative (when taken before receiving antibiotics).

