#### 2.3.2 Secondary Objectives

# STATISTICAL ANALYSIS PLAN for COMPaRE-trial

Our secondary objectives are to investigate the efficiency and costs-effectiveness of the reusable catheter and to explore patient opinions on the reusable catheter. The table below provides an overview of all objectives and outcome measures.

| Objectives                                                                                                                        | Primary outcome | Secondary outcome                                                                                                                                                                                                                                                          | Measured by                                                                                                                                                                                                                  |
|-----------------------------------------------------------------------------------------------------------------------------------|-----------------|----------------------------------------------------------------------------------------------------------------------------------------------------------------------------------------------------------------------------------------------------------------------------|------------------------------------------------------------------------------------------------------------------------------------------------------------------------------------------------------------------------------|
| Safety
To determine whether reusable catheters are at least not less safe as single use catheters                       | No of sUTIs     | 
 
▶ Hospitalisation due to a sUTI
 
▶ Bacteraemic UTI
 
▶ Urethral damage leading to clinical significant strictures
 
▶ Kidney/bladder stone formation
 
▶ Episodes of macroscopic haematuria
 
 | 
 
▶ sUTI (see definition)
 
▶ sUTI +hospitalisation records
 
▶ sUTI +positive blood culture
 
▶ Anamnestic
 
▶ Anamnestic
 
▶ Anamnestic
 
 |

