## 5.3 Secondary Outcomes Definitions

### 5.3.1 Hospitalisation due to UTI

Hospitalisation due to UTI is defined as an admission to a hospital for the management and treatment of a UTI (see primary outcome definition). This occurs when the infection is severe enough to require inpatient care, either due to complications or the inability to manage symptoms adequately in an outpatient setting.

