### 5.3.2 Bacteraemic UTI/ urosepsis

Bacteraemic UTI refers to a UTI associated with bacteraemia, meaning the presence of bacteria in the bloodstream that has originated from the urinary tract. The diagnosis of a bacteraemic UTI is confirmed by blood cultures showing a pathogen typically associated with UTI, alongside clinical symptoms of a UTI. Urine cultures may also provide supportive evidence. The bacteraemia must be determined to have originated from the urinary tract, based on clinical judgment and/or laboratory investigations.

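### SAP 5.2 drops the protocol's blood-culture route to a UTI, and the SAP's two rules for bacteraemic UTI do not agree

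*Combined protocol and SAP*

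**What the plan says.** - **SAP 5.2 (primary outcome).** "An UTI is defined by the following two criteria": symptoms, and "One of the following positive diagnostic tests: urine culture, dipslide, nitrite test, or urine sediment analysis". All four tests are urine tests, and the section sets no rule on timing relative to antibiotics.
- **Protocol 8.1.1, symptomatic UTI.** After the urine tests it adds "or a positive blood culture for a known uropathogen". Negative urine results are considered when the sample preceded antibiotics.
- **Protocol 8.1.1, bacteraemic UTI.** A blood culture growing a known uropathogen, "providing that their urine culture was not negative (when taken before receiving antibiotics".
- **SAP 5.3.2 (bacteraemic UTI).** Blood culture with symptoms confirms the diagnosis, and urinary origin is judged clinically or by laboratory. On urine it says only "Urine cultures may also provide supportive evidence".
- **SAP 2.3.2 (objectives table).** The same outcome is measured as "sUTI +positive blood culture".
- **SAP 5.3.1 (hospitalisation).** Defined as "an admission to a hospital for the management and treatment of a UTI (see primary outcome definition", so it inherits the test requirement of SAP 5.2.

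**The concern.** The SAP is meant to supplement the protocol, and SAP 5.2 names the same definition sources as protocol 8.1.1. Yet it leaves out one qualifying result and the qualifier about antibiotics, without giving a reason. The gap falls on the severe end of the spectrum: urosepsis is the one expected serious event that protocol 9.2.2 names, and protocol 8.1.1 lists admission for a symptomatic UTI beside the UTI itself as a main outcome parameter.

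Protocol 8.1.1 leaves the diagnosis to the local consultant, but SAP 5.2 does not repeat this, so nothing in the SAP settles such an episode. The trial is unblinded. A choice between two rules for a rare outcome should not be left until results by arm can be seen.

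**Working it through.** The plan gives no figure on this point, so there is none to reproduce. The check has two parts.

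**1. Classification.** Take one symptomatic episode with a uropathogen in blood, judged to be of urinary origin. I read sUTI in the 2.3.2 table as the UTI of SAP 5.2, and the blood culture in protocol 8.1.1 as an alternative qualifying result, although that sentence is hard to parse.

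| Urine result | SAP 5.2 UTI | SAP 5.3.1 (if admitted) | SAP 5.3.2 (confirmation sentence) | SAP 2.3.2 table | Protocol bacteraemic UTI |
|---|---|---|---|---|---|
| Any listed test positive | yes | yes | yes | yes | yes* |
| No urine test done | no | no | yes | no | yes |
| Negative, all taken after antibiotics | no | no | yes | no | yes |
| Culture negative before antibiotics, no other test positive | no | no | yes | no | no |

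*Unless a urine culture taken before antibiotics was negative.

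Rows two and three are the discrepancy. The protocol also counts these episodes as symptomatic UTIs; SAP 5.2 does not. In row four the protocol's own bacteraemic definition excludes the episode, so a repair should not simply admit everything that meets 5.3.2.

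**2. Size in the primary outcome.** SAP 6.1.2 divides total UTIs by total follow-up time in each arm. Inputs: 152 evaluable patients per arm and planning rates of 0.13 and 0.14 per month (SAP 6.3); margin 7%, that is 0.07 per month (SAP 3.3.3 and 6.1.2). Assumption: all 152 are followed for 12 months.

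- Follow-up per arm: 152 x 12 = 1824 patient-months.
- Expected UTIs: 1824 x 0.13 = 237 and 1824 x 0.14 = 255.
- Shift per uncounted episode in one arm: 1/1824 = 0.00055 per month. With all 193 randomised per arm: 1/2316 = 0.00043.
- Three, five or ten uncounted episodes in one arm: 0.0016, 0.0027 or 0.0055 per month.
- Episodes needed in one arm to equal the margin: 0.07 x 1824 = 128.

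The documents do not say how often such episodes occur. As an illustration only, assume that 1% to 3% of UTIs are bacteraemic and that one third to one half of those lack a positive urine test. At the mean rate of 0.135 there are 1824 x 0.135 = 246 UTIs per arm. The loss is then 246 x 0.01 x 1/3 = 0.8 to 246 x 0.03 x 1/2 = 3.7 episodes per arm.

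- Lost from one arm only, the upper figure is 3.7/1824 = 0.0020 per month, about 3% of the margin.
- Lost in the same proportion (1.5%) from both arms, it shrinks the planning difference of 0.01 by 0.00015.

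**The case against.** The strongest objection is that the SAP can be read consistently. SAP 5.3.2 opens by describing a bacteraemic UTI as a kind of UTI. Taken with the 2.3.2 table, it becomes a subset of UTI, and the blood culture merely confirms the bacteraemia. On that reading no bacteraemic UTI exists outside the primary outcome. This stands as far as it goes: a reader might infer that the SAP definitely counts such an episode as bacteraemic while denying that it is a UTI, but that follows only from the confirmation sentence in 5.3.2. The consistent reading has its own cost, because it removes from all three outcomes an episode that the protocol counts.

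Other points also stand:

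- Criterion 2 needs only one of four tests. A sterile culture alone does not exclude an episode; all four must be negative or not done. Patients who catheterise four to six times a day can usually supply urine.
- It is the episode that scores zero, not the patient, who may have other UTIs.
- A reader might infer a material bias towards non-inferiority. Proportionate loss does shrink a difference, but the amounts above are negligible, and the documents do not show that losses would be proportionate or heavier in the reusable arm.
- A reader might infer that severe events vanish from the report. An emergency admission for urosepsis would ordinarily still appear in the separate SAE table of SAP 6.1.4 and 7.1. The SAP sets no margin for hospitalisation or bacteraemic UTI.

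**Conclusion.** The concern holds as a definition mismatch. SAP 5.2 omits a route to a UTI that protocol 8.1.1 provides, SAP 5.3.1 inherits the omission, and SAP 5.3.2 and the 2.3.2 table disagree on bacteraemic UTI when no urine test is positive. It does not threaten the primary non-inferiority conclusion: 0.00055 per month per episode, assuming 152 patients per arm with full follow-up, against 0.07. The value of correcting it lies in the two rare severe outcomes, where one or two reclassified episodes are a noticeable share of the count. How many episodes are affected cannot be told from the documents. The conclusion on wording does not depend on that number.

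**What to change.** Before database lock, and without sight of results by arm:

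1. In SAP 5.2 criterion 2, restore "or a positive blood culture for a known uropathogen", subject to the protocol's proviso that a urine culture taken before antibiotics was not negative.
2. Put the same proviso in SAP 5.3.2, and say there that a negative urine result obtained only after antibiotics began does not cancel the event.
3. In the SAP 2.3.2 table, replace the entry for bacteraemic UTI with a reference to 5.3.2.
4. Confirm that SAP 5.3.1 follows the amended 5.2, and clarify the sentence in protocol 8.1.1, so that all five places agree and every bacteraemic UTI is also a UTI.

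Adopting 5.3.2 without the proviso would bring into the primary outcome episodes that the protocol's bacteraemic definition excludes.

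The cost is a few lines of SAP text and perhaps a few more events counted. Sample timing relative to antibiotics must be checked for these episodes. The documents do not show that it is recorded routinely, so source records may be needed.
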